**10.2** **A target number of subjects and rationale for setting the number**

The target number of subjects: 20

［Rationale] Based on the results of the present study on cognitive function and quality of life, a larger-scale validation study is planned in the future. Therefore, this study is an exploratory study, and the number of patients was set at 20 which is the maximum number of patients that can be conducted at the relevant institution. If the intervention in this study has an effect size of 1.4 on the CogEvo change, the probability of error for Type 1 and Type 2 can be assessed as 0.05 and 0.2 respectively with 20 analysis subjects.

**10.3** **Dealing with subjects**

After all subjects have been assessed and prior to analysis, the principal investigator, data management officer and statistical analysis officer will review and record all subjects enrolled in the study, if necessary.

**10.4　Data handling**

If any doubts arise regarding the handling of data during data compilation and analysis, the principal investigator and the statistical analyst will discuss and decide on the handling of the data. Missing values will not be supplemented in principle.

**10.5** **Statistical analysis items and analysis plan**

**10.5.1** **Analysis of study subject background**

Summary statistics for background factors are calculated for the subject population of the efficacy analysis. Specifically, the mean, standard deviation, minimum, median and maximum values are calculated for continuous data, and the number and percentage of persons at each level for classified data.

**10.5.2** **Analysis of primary outcomes**

Group differences in change from baseline on the five cognitive domains (spatial cognition, orientation, memory, attention and executive function) scores of the CogEvo ®︎ will be assessed by analysis of covariance. The significance level is set at 0.05. Missing values are complemented by the last observed value.

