**5.1　Primary　outcome and secondary outcome**

5.1.1　Primary outcome

Assessment of five cognitive domains by CogEvo®︎: spatial cognition, orientation, memory, attention and executive function.

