**5.3** **Methods of case registration and allocation**

The principal investigator (co-investigator) explains the subject of the study in accordance with the explanatory document and, if consent is obtained, registers and allocates the subject as a research participant. Research participants will be given an identification code for anonymization purposes, which will be used as the identification code for research participants in this study.

The study will be conducted in a randomized comparison to ensure that the allocation does not result in differences in medical background between treatment groups. The participants will be allocated in a 1:1 ratio to the SoroTouch treatment group and the non-treatment group using Muzinwali (https://mujinwari.biz/users/login). The allocation method will be stratified block allocation with CogEvo®︎ (index below and above 70) as allocation factor. After obtaining consent from the study participants, investigators will access Muzinwali to confirm the allocation of the intervention to the study participants concerned. As soon as possible after confirming the allocation, the 'Allocation Instructions/Confirmation Form' is signed and dated. After obtaining consent from the research subject to participate in the research and conducting the allocation, the investigator in charge of the research should ensure that all 'allocation instructions/confirmation forms' are properly kept by the principal investigator.

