**8.2　 Evaluation of Efficacy**

8.2.1.　Primary outcome

The intervention is deemed effective if there is a statistically significant difference in changes of CogEvo®︎ scores between the intervention and control groups.

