8.2.2.　Secondary outcome

The intervention is deemed effective if there is a statistically significant difference in changes of SF-36 or MoCA-J scores between the intervention and control groups.

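### Five CogEvo domain scores are primary at an unadjusted 0.05 with no rule on which decides, yet the sample-size section claims error rates of 0.05 and 0.2 as for one test

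*Protocol*

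**What the plan says.** - **Outcome.** Section 5.1.1, repeated in 8.1, defines the primary outcome as five CogEvo domains: "spatial cognition, orientation, memory, attention and executive function". No domain or composite is singled out.
- **Test.** Section 10.5.2 assesses "Group differences in change from baseline on the five cognitive domains (spatial cognition, orientation, memory, attention and executive function) scores of the" CogEvo by analysis of covariance. It adds: "The significance level is set at 0.05". It gives no ordering, composite or adjustment and names no decisive month.
- **Verdict.** Section 8.2.1: "The intervention is deemed effective if there is a statistically significant difference in changes of CogEvo" scores between the two groups. It does not say how many domains must be significant. Section 8.2.2 attaches the same verdict to the secondary outcomes, on a "statistically significant difference in changes of SF-36 or MoCA-J scores between the intervention and control groups".
- **Sample size.** Section 10.2 sets 20 subjects. It states type 1 and type 2 error of 0.05 and 0.2 if the intervention "has an effect size of 1.4 on the CogEvo change", written as one quantity.
- **Status.** Sections 4 and 10.2 call the study exploratory. Section 10.2 says that 20 is the most the institution can manage and that a larger validation study is planned.
- **Changes.** The opening of section 10 requires a protocol revision if the analysis plan departs from the one in the protocol.

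**The concern.** The sample-size section describes one comparison, while the outcome and analysis sections describe five. The verdict section links them without a decision rule. The 0.05 and 0.2 in section 10.2 can belong only to a single prespecified test, and the protocol names none.

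What the trial may claim on its primary outcome is at stake. A chance difference in one of five domains could be reported as effectiveness and carried into the design of the larger study. If the sponsor instead intended all five domains to be significant, the trial is weaker than section 10.2 says.

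**Working it through.** **Inputs from the protocol.** Five primary scores (5.1.1, 10.5.2); level 0.05 (10.5.2); effect size 1.4, type 2 error 0.2, N = 20 (10.2); 1:1 allocation, so 10 per arm (5.3).

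**Assumptions, not in the protocol.** Two-sided tests; one time point; a common correlation rho between domains, shown from 0 to 0.9.

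**Step 1: reproduce the plan's figure.** For one two-sample t-test at two-sided 0.05, the noncentrality is 1.4 × √(n/2) with 2n − 2 degrees of freedom. Power is 79.6% at 9 per arm and 84.1% at 10 per arm. The smallest n reaching 80% is therefore 10 per arm, or N = 20. Using the 17 degrees of freedom of an analysis of covariance gives 83.9%. Section 10.2 is correct for a single comparison.

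**Step 2: any one of five suffices.** With independent domains, the chance of at least one false significant difference is 1 − 0.95^5 = 22.6%. Counting only differences favouring SoroTouch, it is 1 − 0.975^5 = 11.9%, against a nominal 2.5%. Simulation with 10 per arm gives the values for correlated domains:

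| rho | Either direction | Favouring SoroTouch |
|---|---|---|
| 0 | 22.6% | 12% |
| 0.5 | 18% | 9% |
| 0.7 | 15% | 8% |
| 0.9 | 10% | 5% |

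Simulating the full analysis of covariance gives similar two-sided values: 22.7%, 19.9%, 16.0% and 10.6%.

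**Step 3: all five required.** Type 1 error is not inflated. If every domain truly has effect size 1.4, power with independent domains is 0.841^5 = 42%. By simulation it rises to about 74% at rho 0.9, still short of 80%.

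**Step 4: adjusted testing.** Bonferroni gives 0.05/5 = 0.01 per domain.
- For one pre-chosen domain at effect size 1.4 and 10 per arm, power is 60%. Reaching 80% needs an effect size of 1.69, or 14 per arm (N = 28).
- For at least one significant domain when all five respond at 1.4, power is about 99% at rho 0, 91% at 0.5, 85% at 0.7 and 75% at 0.9.

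The power of an adjusted rule therefore depends on how many domains are assumed to respond and how correlated they are. Section 10.2 states neither.

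**The case against.** The strongest reply is that the study is exploratory, limited to 20 subjects by capacity, and to be followed by a larger study. Unadjusted testing of several outcomes is common in such work. This stands in part and lowers the severity. It does not make the quoted 0.05 correct while sections 8.2.1 and 8.2.2 turn significance into a verdict of effectiveness.

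A second reply is that the statistical analysis plan may settle the matter. But the outcome, level, verdict and power basis are fixed in the protocol, and section 10 itself requires a protocol revision to change the analysis.

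Some stronger readings are tempting but not supported:
- **That the protocol lays down an any-of-five rule.** This is the natural reading, and the word "or" in section 8.2.2 points the same way, but section 8.2.1 does not say it. The documented fault is an undefined rule.
- **That the true type 1 error is 15% to 23%.** That range needs correlations between 0 and about 0.7, which the protocol does not give, and it counts differences favouring control. The chance of a false claim of benefit is about half as large.
- **That secondary outcomes should be pooled into the error rate.** Section 10.2 ties its 0.05 to CogEvo only, and the protocol does not state how many SF-36 scales would be tested.
- **That adjustment cuts power to 60%.** This holds only for one pre-chosen domain.
- **That an overall CogEvo index is ready to serve as primary.** Section 5.3 mentions only an "index below and above 70) as allocation factor". It does not say that the index combines the five domains or is available at month 6.

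**Conclusion.** Wrong as written; should be fixed. The error rates in section 10.2 are those of a single test and belong to neither reading of the rule in 8.2.1 and 10.5.2.

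Under any-of-five, the two-sided false-positive chance is two to four and a half times the stated 0.05 (10% to 22.6% for rho from 0.9 down to 0). In SoroTouch's favour it is about 5% to 12%, against 2.5%. Under all-five, the error is controlled but power falls short of 80% across the same correlations, even if all five domains have the full effect of 1.4.

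These figures count one time point. Section 8.3 speaks of monthly analysis and no decisive month is named, so a reader might infer further inflation. The protocol does not say that each month is tested towards the verdict, so no figure is put on it.

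**What to change.** Reword sections 5.1.1, 8.2.1, 10.2 and 10.5.2 to name one primary CogEvo score at one time point, for example month 6, tested once at two-sided 0.05. Report the other domains as supportive, with estimates and 95% confidence intervals. The effect size and error rates in 10.2 then fit the rule, provided that 1.4 is meant for that score. The index used for stratification may serve only if the sponsor confirms that it is an overall score available at that time point.

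If all five domains must stay primary, apply Holm and restate in 10.2 the power for that rule, with the assumed number of responding domains and their correlation.

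In either case, remove the effectiveness verdict from section 8.2.2.

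The cost is a protocol revision, with no new data if the chosen score is already collected at that time point. The downside is that an isolated single-domain result could no longer be called effectiveness; under Holm, only a domain that passes the adjusted test could be.

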**6.4　 Criteria for discontinuation for each research participant**

If any of the following events occur during the research period, the investigators will discontinue the research on the relevant research participants. When the investigators decide to discontinue or suspend the research, the investigators will take appropriate action to deal with the research participants.

1) If the research participant (or surrogate) asks to discontinue the research.

2) If the research participant discontinues participation in the research for personal reasons (e.g. moving, changing doctor or hospital, busy schedule, inability to follow up, etc.)

3) If the research participants are found to be unsuitable for the subjects after the start of the research

4) If an accidental incident occurs

5) If an adverse event occurs (including exacerbation of the underlying disease, complications or accidental injury) and the investigator decides that the study should be discontinued

6) If it becomes difficult to continue the research due to ill health

7) When there is a serious deviation from the research protocol and it is judged that the research cannot be evaluated

8) When it is found that the research participant is not carrying out the task as instructed by the investigators

9) In other cases where the investigators judge that it is difficult to continue the research and that discontinuation is appropriate.

［Rationale]

This criterion was set in order to ensure the ethical and safe implementation of the research and to ensure the safety of the research participants.

[Methods of action at the time of discontinuation]

After discontinuation, observation will not be continued.

1. **Medical treatment of the clinical research participants**

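### Sections 10.4 and 10.5.2 give unreconciled rules for missing CogEvo values, and carrying the last value forward suits a monthly measure of change badly

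*Protocol*

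**What the plan says.** Two sections of the protocol deal with missing values.

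- Section 10.4, on data handling in general: "Missing values will not be supplemented in principle".
- Section 10.5.2, on the primary outcome: "Missing values are complemented by the last observed value". The same section says that group differences in change from baseline on the five CogEvo domain scores "will be assessed by analysis of covariance".

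Neither section refers to the other, and 10.5.2 is not labelled an exception. Section 10.5.3, on the secondary outcomes, gives no missing-data rule.

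Other sections determine how much data will be missing and in whom:

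- CogEvo is given at baseline and at each of months 1 to 6 (5.2.2, 10.6).
- Section 6.4: "After discontinuation, observation will not be continued". Its eighth criterion allows discontinuation of a participant who is not doing the task as told.
- Sections 5.2.2 and 10.6 limit the analysis of people who average under 10 minutes of learning a day to the periods above that level. Section 10.6 then adds that all assessed data are to be used.
- Section 10.1.1 keeps anyone with some intervention and at least one later assessment, so partial drop-outs enter the primary analysis.

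**The concern.** The primary analysis should be executable in one way only. Here an analyst who follows 10.4 and one who follows 10.5.2 would analyse different numbers of people. Section 10.4 leaves doubts about data handling to the principal investigator and the analyst during compilation and analysis, and section 7.1 gives random allocation and statistical analysis to the same person. A choice left open may therefore be made late, with allocation known. A separate analysis plan would not settle it quietly: section 10 requires a protocol revision if the analysis departs from what the protocol sets out.

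The second issue is the method. LOCF supposes that a score stays where it was at the last visit. A test given seven times over six months, in a trial of training, may well move through practice, training or decline. Only the app arm has a daily training task, so discontinuation for not doing it and the 10-minute rule fall mainly on that arm. If drop-out is unequal, LOCF freezes the scores of more people in one arm than in the other. The protocol also does not say whether months below 10 minutes count as missing. If they do, LOCF would overwrite real scores with older ones.

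At stake is the estimate that section 10.2 wants for planning a larger study.

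**Working it through.** **1. The plan's own figure.** Section 10.2 takes an "effect size of 1.4 on the CogEvo change" and says that "the probability of error for Type 1 and Type 2 can be assessed as 0.05 and 0.2 respectively with 20 analysis subjects". A two-sided two-sample t-test with effect 1.4, alpha 0.05 and power 0.80 needs 9.08 per arm, rounded up to 10 per arm, or 20 in all; power at 10 per arm is 0.841. (Sidedness is not stated; two-sided is assumed.) The figure reproduces, so this point does not rest on a sample-size error. But 20 is both the target and the number analysed, so there is no allowance for loss.

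**2. The two rules on the same data.** If 3 of 10 app participants leave before month 6, a month-6 analysis has 20 people under 10.5.2 and 17 under 10.4.

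**3. LOCF with no true effect.** The documents give no practice gain, drop-out rate or drop-out timing, so these are assumptions. Let g be a common linear gain over 6 months in SD units, d_app and d_con the drop-out proportions, and m the mean month of the last visit. Each drop-out loses f = (6 − m)/6 of the gain, so

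shift in month-6 difference = −(d_app − d_con) × g × f.

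Last visit spread evenly over months 1 to 5 gives m = 3 and f = 1/2. Last visit at months 1 to 3 gives m = 2 and f = 2/3.

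| g | d_app − d_con | f = 1/2 | f = 2/3 |
|---|---|---|---|
| 0.3 | 0.20 | −0.03 | −0.04 |
| 0.3 | 0.30 | −0.045 | −0.06 |
| 0.5 | 0.20 | −0.05 | −0.067 |
| 0.6 | 0.30 | −0.09 | −0.12 |
| 0.8 | 0.30 | −0.12 | −0.16 |
| 1.0 | 0.30 | −0.15 | −0.20 |

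The shift is zero if g = 0 or drop-out is equal. It changes sign if controls drop out more, or if scores decline on average (g below 0).

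**4. LOCF with the protocol's effect of 1.4, growing linearly, f = 1/2, g = 0.6.**

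- 30% versus 0% drop-out: app arm (0.6 + 1.4) × (1 − 0.30 × 0.5) = 1.70; control 0.60; difference 1.10.
- 20% in both arms: app arm 2.0 × 0.90 = 1.80; control 0.6 × 0.90 = 0.54; difference 1.26. So a growing effect is attenuated even with equal drop-out.

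**5. Simulation check** (10 per arm, SD 1, 4,000 runs, t-test on change standing in for the analysis of covariance, drop-out at random).

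| Setting (g = 0.6) | LOCF estimate | LOCF rejection rate | Observed-case estimate | Observed-case rejection rate |
|---|---|---|---|---|
| No effect, 3 vs 0 lost | −0.086 | 0.057 | −0.001 | 0.048 |
| Effect 1.4, 3 vs 0 lost | 1.102 | 0.587 | 1.402 | 0.755 |
| Effect 1.4, 2 vs 2 lost | 1.259 | 0.703 | 1.402 | 0.735 |

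Across the null settings run (g of 0.6 or 1.0), LOCF rejected in 0.054 to 0.061 of runs. The observed-case estimates are unbiased here only because drop-out was simulated at random.

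**The case against.** **The rules may not conflict.** The closing qualifier in 10.4 makes its rule a default, and 10.5.2 is a specific rule for one outcome. Read together they are coherent: LOCF for CogEvo and nothing filled in elsewhere. This stands as a fair reading, and probably the natural one. A reader might infer two flatly opposite rules; the qualifier does not support that. What remains is that the protocol never states the exception, and that this reading still leaves LOCF in place.

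**The size rests on assumptions.** Also true. If gains level off by months 1 to 3, the null shift is near zero. Unequal drop-out is inferred: the eighth criterion in 6.4 names no arm, section 13.1.2 expects burdens on controls too, and section 15.1 pays everyone.

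**The null shift is small.** At 10 per arm and SD 1 the standard error of the difference is √(2/10) = 0.45, so 0.05 to 0.16 SD is about 0.1 to 0.4 standard errors. With more drop-out in the app arm and rising scores it runs against the app. A reader might infer that LOCF invalidates the standard errors or invites a false positive. The simulation does not show that: rejection under no effect stayed near 0.05. A tilt towards the app needs more drop-out among controls or an average decline; the documents support neither as an expectation.

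**LOCF may suit people who stop training.** The attenuation in step 4 is measured against the difference that would be seen had everyone stayed. If gains stop when training stops, a frozen score is less wrong. The protocol does not say which of these it wants to estimate.

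**Conclusion.** The point holds in a limited form. The missing-data rule for the primary outcome is stated in two places that must be reconciled; this rests on the text alone. LOCF is a poor rule for CogEvo whichever way they are reconciled. The main harm is a distorted, usually attenuated, estimate and lost power, not an inflated error rate.

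The null shift is roughly −0.05 to −0.16 SD over most of the assumed range, with corners at −0.03 and −0.20. An effect of 1.4 falls to about 1.26 or 1.10 in the two settings worked, and in the second power is about 0.59 against 0.76 for observed cases. All of these figures depend on linear change and on assumed drop-out, and those with a true effect also assume that it builds up linearly. None is a forecast for this trial.

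The study is exploratory and sized by feasibility, so this should be fixed before analysis, but it does not by itself undermine the design.

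**What to change.** 1. Delete the LOCF sentence from 10.5.2. Analyse each of the five CogEvo domain scores with a repeated-measures mixed model on all observed monthly values: arm, month, arm by month, baseline score and the allocation stratum from 5.3. State in advance a simple covariance (a random participant intercept or AR(1)) and small-sample degrees of freedom such as Kenward-Roger.
2. Name the month-6 arm difference as the estimate. Section 10.5.2 now gives no time point, so this is an addition.
3. State that collected months below 10 minutes a day are kept as observed data, in line with the closing instruction of 10.6 to use all assessed data, and amend the restricting sentences in 5.2.2 and 10.6 to match.
4. Reword 10.4 so that it agrees: no values are filled in, and the primary analysis uses all observed scores through the model. Keep LOCF at most as a labelled sensitivity analysis.

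The cost is protocol wording and somewhat more analysis work; the monthly scores are already collected. The downside is that the model assumes data missing at random given the observed scores. People who leave through ill health or because they are not training may break that assumption, and observation stops when they leave, so the data cannot test it. With 20 people the model must also stay simple.

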**10.5.3** **Analysis of secondary outcomes**

The MoCA-J and SF36 scores will be compared between the two groups before and at 6 months after the start of Soroouch by an unpaired t-test.

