**8.3** **Method and timing of analysis of endpoints**

Primary outcome

After entry and initial assessment of study participants, eligible data will be analysed every month for a total of six months.

Secondary outcome

Data will be collected at the end of the evaluation period and MoCA-J and SF36 scores analysed between intervention and control groups.

1. **Evaluations of safety**

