**10.6** **Time point of analysis**

For the secondary outcome measures, MoCA-J and SF36 scores, data will be collected during the evaluation period and 6 months after the start of SoroTouch. For the primary outcome, CogEvo®︎, data will be collected during the evaluation period and every month thereafter until 6 months after the start of SoroTouch, and statistical analysis will be performed after the end of the observation period. If there are subjects whose average daily learning time is less than 10 minutes, in principle, the data will be analysed only for the period when they were able to perform the study for more than 10 minutes a day. However, all evaluated data should be used in the analysis. If necessary, subgroup analyses will be conducted according to medical history, diseases being suffered from, medications taken during the intervention period, etc.

The statistical analyst will compile a primary endpoint report and submit it to the principal investigator.

1. **Access to original data**

The principal investigator and the administrator of the implementing medical institution will accept monitoring and investigations by the accredited clinical research review committee and regulatory authorities on this research, and will ensure that all source documents and other materials related to this research are made available for direct inspection at that time.

1. **Quality control and quality assurance**

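### The unpaired t-tests planned for MoCA-J and SF-36 do not test the change on which effectiveness is judged, and they leave the measured baseline unused

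*Protocol*

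**What the plan says.** Three places in the protocol describe the secondary efficacy analysis.

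- **Section 8.2.2** (criterion): the intervention is effective on a secondary outcome if there is a "statistically significant difference in changes of SF-36 or MoCA-J scores between the intervention and control groups".
- **Section 8.3** (timing): "MoCA-J and SF36 scores analysed between intervention and control groups". It does not mention change.
- **Section 10.5.3** (method): the scores are to be "compared between the two groups before and at 6 months after the start of Soroouch by an unpaired t-test".

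The baseline is available. Section 10.6 states, for the "MoCA-J and SF36 scores, data will be collected during the evaluation period and 6 months after the start of SoroTouch", and the schedule in 5.2.2 marks both instruments at the assessment/allocation period and at month 6.

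The primary outcome is treated differently. In 10.5.2, "Group differences in change from baseline on the five cognitive domains" "will be assessed by analysis of covariance". Nothing in the protocol says that the secondary t-test is run on change or adjusted for baseline.

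**The concern.** The criterion concerns change, while the method concerns scores at two separate times. Read as written, 10.5.3 produces two p-values per scale, and neither answers 8.2.2.

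- The baseline comparison tests a hypothesis that randomisation has already made true.
- The month-6 comparison carries any chance baseline difference straight into the result. Allocation is stratified on CogEvo only (section 5.3), so MoCA-J and SF-36 are not directly balanced.

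What is at stake is which result decides whether the app is called effective on cognition screening or quality of life. Section 10.2 says that the results on cognitive function and quality of life will feed a larger study, so the precision of these estimates matters.

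**Working it through.** **Inputs.** From the protocol: 10 per arm (5.2.2; 1:1 in 5.3) and "The significance level is set at 0.05" (10.5.2). Assumed: a two-sided test, the 0.05 level also for the secondary outcomes, normal scores with equal SD at both times, and no missing data. The protocol gives no effect size for MoCA-J or SF-36 and no baseline-to-month-6 correlation *r*, so I use a difference of 1.0 SD of the month-6 score and a range of *r*.

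**The protocol's own figure.** Section 10.2 reads "If the intervention in this study has an effect size of 1.4 on the CogEvo change", with errors of 0.05 and 0.2 and 20 subjects. For an unpaired t-test the noncentrality is d√(n/2). With d = 1.4 and n = 10 it is 1.4 × √5 = 3.13 on 18 df, which gives power 0.841. At 9 per arm the power is 0.796. Ten per arm is therefore the smallest size that reaches 80%, and the stated figure reproduces. It applies to CogEvo, not to the secondary scales.

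**Three analyses at 10 per arm, difference 1.0 SD**

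1. *Month-6 t-test.* Noncentrality 1.0 × √5 = 2.24, power 0.562 whatever *r* is.
2. *t-test on change.* The variance of change is 2(1−r) in units of the score variance, so the standardised effect is 1/√(2(1−r)). At r = 0.7 it is 1/√0.6 = 1.29.
3. *ANCOVA on baseline.* The residual variance is (1−r²) and the residual df are 17. Power is by simulation (40,000 trials per cell).

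| r | Month-6 t-test | Change t-test | ANCOVA |
|---|---|---|---|
| 0 | 0.562 | 0.322 | 0.535 |
| 0.3 | 0.562 | 0.432 | 0.579 |
| 0.5 | 0.562 | 0.562 | 0.658 |
| 0.7 | 0.562 | 0.779 | 0.816 |
| 0.8 | 0.562 | 0.916 | 0.925 |

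At a difference of 1.4 SD the month-6 t-test has 0.841. ANCOVA has 0.851, 0.910, 0.979 and 0.997 at r = 0.3, 0.5, 0.7 and 0.8.

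**Variance ratio, month-6 comparison to ANCOVA.** In large samples it is 1/(1−r²): 1.33, 1.96 and 2.78 at r = 0.5, 0.7 and 0.8. With 10 per arm, estimating the slope inflates the ANCOVA variance by 1 + 1/(2n−4) = 1 + 1/16 = 1.0625. The ratios then become 1.33/1.0625 = 1.25, 1.96/1.0625 = 1.84 and 2.78/1.0625 = 2.61.

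**Chance imbalance at baseline.** If allocation is unrelated to these scales, the baseline mean difference has standard error √(2/10) = 0.447 SD. An imbalance above 0.5 SD corresponds to |Z| > 0.5/0.447 = 1.12, which has probability about 26%.

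**Does the choice change the verdict?** With a 1.0 SD difference and r = 0.7, the month-6 test and the change test disagree on significance in about 38% of simulated trials. With no true difference, every analysis, including the baseline test, is significant in about 5% of trials.

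**The case against.** The strongest reply is that 10.5.3 is a loose translation and means the before-to-month-6 change, compared between arms by an unpaired t-test. The sentence can bear that reading, and it would then agree with 8.2.2. Most of the power gap would also close at high correlation: 0.779 against 0.816 at r = 0.7, and 0.916 against 0.925 at r = 0.8. However, the text does not say this, and 8.3 also speaks only of scores. The wording needs correcting on either reading. A change-score t-test is also the weakest of the three analyses when the correlation is low (0.432 against 0.579 for ANCOVA at r = 0.3).

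Other points stand as limits on the concern:

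- The month-6 t-test keeps its 5% error rate under randomisation. Chance imbalance is already in its standard error, so this is imprecision and not bias.
- The gain from ANCOVA depends on *r*. It is negligible at 0.3, and there is a small loss at 0 (0.535 against 0.562).
- At 1.4 SD the month-6 test already has 0.841.
- Adding the CogEvo stratum costs a further degree of freedom. If the stratum is unrelated to the outcome and unbalanced between arms, ANCOVA power is about 0.55, 0.63, 0.79 and 0.90 at r = 0.3, 0.5, 0.7 and 0.8. Because allocation is stratified, that is pessimistic; with a balanced stratum, power is almost unchanged.
- These are secondary outcomes in an exploratory trial, and no power is claimed for them.

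It could also be said that covariates belong in a statistical analysis plan. Here, though, the protocol has fixed the test itself. The opening of section 10 requires a protocol revision if the analysis plan departs from it, so a separate plan should not silently override 10.5.3.

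**Conclusion.** The concern holds. The method in 10.5.3, as written, does not test the quantity in 8.2.2, and it leaves unused a baseline that is collected anyway. Under the assumptions above, the cost against ANCOVA at a 1.0 SD difference is about 10 percentage points of power at r = 0.5, 25 at r = 0.7 and 36 at r = 0.8. It is next to nothing at r = 0.3 and reverses slightly at r = 0. The conflict between the sections does not depend on *r*. The issue should be corrected, but it does not threaten the validity of the trial.

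**What to change.** Replace 10.5.3 with a statement to this effect: *Month-6 MoCA-J and SF-36 scores will be compared between arms by analysis of covariance, adjusted for the baseline score of the same scale and the CogEvo allocation stratum, and reported as an adjusted mean difference with 95% confidence interval.* Remove the baseline significance test; the descriptive summary in 10.5.1 is enough for baseline.

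Align 8.2.2 and 8.3 to this estimate. With the baseline score as covariate, ANCOVA of the month-6 score and ANCOVA of the change give the same treatment effect, so the reference to change in 8.2.2 can be kept if it is defined this way.

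The cost is a short protocol revision and one or two residual degrees of freedom. No additional data or visits are needed.
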